### Study objectives

Primary objectives:
To identify monthly recruitment rates to determine whether it is possible to enrol at least one patient per month from each study centre.To report participant adherence to ARC intervention and control treatment arms (provider observation and exercise diaries).To assess the acceptability and completeness of proposed methods of data collection to ensure they are feasible for a definitive trial.

Secondary objectives:
4.To report participant retention to the study.5.To report the success of outcome assessor blinding to participant treatment allocation.6.To report adverse events in control and intervention treatments during the study.7.To report the views of study participants about undertaking the ARC intervention at home and in the community.8.To report the views of providers and clinical therapists about the study protocol.9.To gather data to allow reporting of summary statistics to allow estimation of the sample size requirements for the definitive trial.

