### Progression criteria

Progression criteria have been set based upon recruitment, treatment adherence and data completeness to determine whether progression to a definitive trial is appropriate. These criteria and the traffic light system applied are based upon recommendations from Avery et al. [20].

Potential success criteria:
*Recruitment of participants*: green = an average of at least four patients per month recruited across the four sites; amber = an average of at least three patients per month recruited across the four sites; red = two or fewer patients recruited per month across the four sites.*Treatment adherence*: green = an average of at least 80% (840 out of 1080) supervised and self-monitored treatment sessions completed across the intervention and control treatment cohorts measured by provider observation and exercise diaries; amber = an average of at least 70% (756 out of 1080) supervised and self-monitored treatment sessions completed by participants; red = an average of 70% or less supervised and self-monitored treatment sessions completed by participants.*Data completeness:* green = completion (no missing data) of over 85% of key outcome measures (7 day accelerometer measurement; walking speed in the home; miniBEST and self-completion questionnaires: for full description see the ’Baseline assessment’ section) at 10-week outcome assessment for all those completing the treatment programmes; amber = completion of over 70% of key outcome measures at 10 weeks; red = completion of 70% or less of key outcome measures at 10 weeks.

Whilst these criteria will be used to evaluate the likely feasibility of a larger trial, they will primarily be employed to optimise the study design and identify/address issues in order to take remedial steps in a timely fashion. An example of this would be problems around recruitment.

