## Methods

### Study design

This study is a pilot multi-centre, observer blind, parallel group randomised controlled trial (RCT), with an allocation ratio of 1:1.

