### Sample size

We aim to recruit 60 participants in 15 months at a rate of one patient per trial centre per month. This sample size has been selected as it is the sample recommended for pilot studies [21]. We believe that this is a realistic recruitment rate informed by previous trials [22, 23].

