### Study intervention treatment: auditory rhythmical cueing and gait and balance exercises

#### Dose and duration

Participants will be asked to undertake three × 30-min ARC treatment sessions per week for 6 weeks (total 18 sessions). This dose and duration has been selected based on findings from previous laboratory-based studies investigating cueing after stroke [11] and on findings from our previous successful RCT in Parkinson’s disease [24].

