### Study control treatment: gait and balance exercises

#### Dose and duration

Control participants will undertake a matched dose of balance and gait exercise treatment sessions to the intervention treatment group, e.g. three × 30-min sessions per week for 6 weeks (total 18 sessions).

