### Data analysis

Objectives 1–3: Recruitment will be described as rate/month (total and per site). Adherence will be described using data from the exercise diaries (number of planned sessions completed). Acceptability and completeness of methods of data collection will be described using percentages from both treatments.

Objective 4: Retention will be described as percentage from both treatments.

Objective 5: The success of outcome measurement blinding will be described (%).

Objective 6: Adverse events pertaining to the study for each treatment will be described (number of events).

Objective 7: The views of study participants about undertaking the ARC treatment at home and in the community will be described. Summary statistics will be used for answers to closed questions and open questions will be thematically analysed.

Objective 8: The views of providers and clinical therapists about delivery of the study treatments will be described. Summary statistics will be used for answers to closed questions and open questions will be thematically analysed.

Objective 9: As this is a pilot study, statistical comparisons of clinical outcomes (e.g. dynamic gait index, see above) and accelerometer data between treatments will not be undertaken and data will be presented as summary descriptive statistics. To determine which outcome measures to take forwards to a main trial, we plan to review data completeness, patient/staff feedback about acceptability and any new emerging literature about most appropriate measures, to inform decisions. This review will also determine the most appropriate primary outcome measure. Data collected for this selected primary outcome measure (e.g. standard deviation) will subsequently be used as appropriate by statisticians to inform a power calculation for a definitive trial.

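### The adherence criterion pools both arms with no floor for either, so it can score green while ARC adherence is at or below 70%

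*Protocol article*

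**What the plan says.** Under Progression criteria, green for adherence is an average of at least 80% of "supervised and self-monitored treatment sessions completed across the intervention and control treatment cohorts". Amber is at least 70% and red is 70% or less. The green and amber counts are both printed out of 1080. No minimum is set for either arm.

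The objectives are worded at a finer level. Primary objective 2 is "To report participant adherence to ARC intervention and control treatment arms". Primary objective 1 asks "whether it is possible to enrol at least one patient per month from each study centre", whereas every recruitment band is an average over the four sites together.

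The Data analysis section states: "Recruitment will be described as rate/month (total and per site". Its sentence on adherence refers to planned sessions completed according to the diaries and mentions no split by arm. Neither statement is linked to the traffic lights.

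The Progression criteria section calls the criteria potential ones. It says that they bear on whether a definitive trial is appropriate, and that their main use is to improve the design and put problems right.

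**The concern.** The study is meant to show whether a trial of ARC training is feasible. The Discussion section puts acceptability and feasibility of the cued programme first. A pooled average does not isolate that. If control participants complete nearly everything and ARC participants leave out a third of their sessions, the pooled figure can still reach 80%. The pre-specified signal would then be green although the new treatment was not being taken up at the level the plan regards as adequate overall. The reverse case, poor control adherence hidden by good ARC adherence, would also matter to a definitive comparison.

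Equal adherence cannot be assumed. ARC involves a device and six supervised sessions, while the weekly control contact may be by telephone.

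The recruitment criterion has a milder form of the same feature: a centre that recruits nobody can be offset by the others.

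**Working it through.** **Inputs**
- Sample size and period (Sample size): "We aim to recruit 60 participants in 15 months at a rate of one patient per trial centre per month".
- Sessions per ARC participant (Dose and duration, intervention): "three × 30-min ARC treatment sessions per week for 6 weeks (total 18 sessions".
- Sessions per control participant (Dose and duration, control): "three × 30-min sessions per week for 6 weeks (total 18 sessions".
- Allocation (Study design): "with an allocation ratio of 1:1", so about 30 per arm.
- Adherence by arm: the documents give no expected value. The control values below are assumptions, shown as a range.

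**The plan's own figures**
- Denominator: 60 × 18 = 1080. Reproduces.
- Amber: 0.70 × 1080 = 756. Reproduces.
- Green: 0.80 × 1080 = 864. The printed count is 840, and 840/1080 = 77.8%. This mismatch is a separate error. The results below use 864, the count that matches the stated 80%.

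**Lowest ARC adherence that still scores green**

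Planned sessions per arm: 30 × 18 = 540. Formula: (864 − control adherence × 540) / 540.

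| Control | ARC sessions needed | ARC adherence |
|---|---|---|
| 100% | 864 − 540 = 324 | 60.0% |
| 95% | 864 − 513 = 351 | 65.0% |
| 90% | 864 − 486 = 378 | 70.0% |

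ARC can therefore be at or below 70% under a green light only if control is at 90% or more, a gap of at least 20 points. If the printed 840 were used, ARC at 70% would need control at (840 − 378)/540 = 85.6%, a gap of 15.6 points.

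**Unequal arms.** Randomisation is simple, so the arms need not be 30 and 30. With 26 ARC and 34 control and control at 90%, ARC needs (864 − 550.8)/468 = 66.9%. With 34 ARC and 26 control, it needs (864 − 421.2)/612 = 72.4%. The limit moves with the split.

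**Bands by arm, at 30 per arm.** Green: 0.80 × 540 = 432. Amber: 0.70 × 540 = 378. ARC at 65% (351 of 540) falls below amber.

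**Recruitment**
- Green needs 4 × 15 = 60 patients in 15 months. Three centres at 4/3 = 1.33 per month and a fourth at zero would reach it.
- Now test a strict rule of at least one per month at every centre. Assume independent Poisson recruitment at exactly the planned rate, with all centres open for 15 months (mean 15 each). One centre reaches 15 with probability 0.534, and all four do so with probability 0.534⁴ = 0.08. The pooled rule (at least 60, mean 60) is met with probability 0.52.
- If recruitment stops at 60, the strict rule needs exactly 15 at each centre. With four equally recruiting centres that has multinomial probability 60!/(15!⁴ × 4⁶⁰) = 0.002.

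**The case against.** Pooling can be defended. The primary aim is feasibility of a parallel-group trial, which needs adherence in both arms. The criteria are called potential and serve mainly to improve the design. Objective 2 covers adherence in both arms and per-site recruitment is to be reported, so a weak arm or centre would probably be noticed. The examples also need a large gap. The arms have matched doses and the same exercises apart from cueing. If an ARC participant attended all six supervised sessions, 60% overall (10.8 of 18) would mean 4.8 of the 12 home sessions, or 40%, against complete adherence in control. The protocol reports good adherence to the intervention in the earlier before-and-after study.

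Most of this stands as a limit on size. It does not remove the point. An average over both arms does not show that each arm is adherent, and the pre-specified colour would still be green, leaving any correction to judgement after the fact.

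A reader might go further in three ways that the documents do not support:
- That ARC would have failed the plan's own red line. The 70% line is defined on the pooled average, and no line exists for ARC alone.
- That green by itself means go. The text does not say so.
- That ARC at 55.6% would pass, from (840 − 540)/540. That figure depends on the printed 840, which is a separate error.

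**Conclusion.** The point holds for adherence, at moderate weight. The criterion pools the arms and sets no floor for either. At 30 per arm and a true 80% cut-off, it can be green with ARC anywhere from 60% to 70%, provided control is correspondingly between 100% and 90%. That is a possible outcome, not a predicted one, since the documents give no expected adherence by arm. The result does not depend on the misprinted count.

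For recruitment, the mismatch between the four-site total and the per-centre objective is real but smaller. Per-site rates are already planned, and hiding one empty centre needs the other three to run a third above plan. A reader might conclude that green should require every centre to average one per month. The calculation argues against that: under the Poisson assumption, a trial recruiting exactly to plan would meet such a rule about 8% of the time.

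**What to change.** **Adherence.** Apply the 80% and 70% bands to each arm separately, with 18 × the number randomised in that arm as the denominator. At 30 per arm this is 540 sessions, with green at least 432 and amber at least 378. Require the ARC arm to meet the band for whatever colour is awarded, and state the control arm's result beside it. Say in the Data analysis section that adherence is reported by arm.

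**Recruitment.** Keep the pooled bands and add no strict per-centre condition. State that the planned per-site rates will be set beside the pooled colour when progression is judged, so that objective 1 is answered directly.

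**Cost.** A change of wording only. Diaries are kept by each participant and recruitment is already to be described by site. The downside is precision: each arm's adherence rests on about 30 people instead of 60, so a colour near a boundary is less certain.

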## Methods

### Study design

This study is a pilot multi-centre, observer blind, parallel group randomised controlled trial (RCT), with an allocation ratio of 1:1.

### Study setting

Participants will be recruited from four NHS community stroke services in the North East of England and from regional community stroke group meetings. The study treatments will be delivered in the participant’s homes and nearby community.

### Study population

Eligibility criteria:

*Inclusion criteria*
Adults (≥ 18 years) with any stroke subtype.Within 24 months of stroke onset.Able to mobilise independently > 10 m with/without stick indoors but presenting with a gait-related mobility impairment (e.g. gait asymmetry, reduced walking speed, reduced balance, reduced walking confidence based on clinical observation or patient subjective feedback) that would potentially benefit from this intervention.Community dwelling and living within the community services catchment area of a participating study centre.Able to provide informed consent to participate in the study.

*Exclusion criteria*
Currently undertaking any active physiotherapy.Unable to follow study treatment due to significant cognitive impairment or communication difficulties.Diagnosis likely to interfere with adherence to treatment or predispose to falls, e.g. uncorrected hearing problems; registered blind; severe visual/inattention problems as a result of stroke; upper limb impairment restricting use of cueing device; able to mobilise 10 metres but extremely slow gait speed limiting intervention adherence.Other neurological or orthopaedic conditions affecting gait (e.g. Parkinson’s disease, multiple sclerosis, osteoarthritis, rheumatoid arthritis and back pain), cardiopulmonary conditions which alter walking ability (e.g. chronic obstructive disorders, angina pectoris) and palliative treatment.

### Sample size

We aim to recruit 60 participants in 15 months at a rate of one patient per trial centre per month. This sample size has been selected as it is the sample recommended for pilot studies [21]. We believe that this is a realistic recruitment rate informed by previous trials [22, 23].

### Case ascertainment recruitment and consent

Eligible patients will be identified by healthcare professionals or by National Institute for Health Research (NIHR) Clinical Research Network (CRN) Clinical Trial Officers (CTO) working within NHS stroke services. CTO’s are part of the hospital stroke team, and there is regular liaison between themselves and other stroke staff to identify patients who may be eligible to be invited to participate in stroke research studies.

Eligible patients will be approached by a healthcare professional or a CTO, a discussion about the study held and an information sheet provided. After allowing sufficient time for this information to be considered, and an opportunity to ask questions, if the eligible patient wishes to take part, they will be asked if they are happy for their details to be shared with the study team. The study team will be alerted and they will contact the patient to provide more information about the study if necessary and arrange a visit to obtain consent in writing. Where a patient is able to provide consent but is unable to sign the consent form (e.g. because of weakness of the dominant hand following stroke), consent will be confirmed orally in the presence of a witness (an individual not otherwise involved in the trial) who will sign the consent form on behalf of the participant.

We will also seek to recruit via advert from community stroke groups within the trial catchment area. On expression of interest, and if eligible, those responding to the advert will be given a participant information sheet and an ‘invitation’ card with study contact names and phone numbers. Their contact details will be taken, and after being given time to consider participating, the study team will contact the potential participant to provide more information about the study and arrange a visit to obtain consent in writing.

The original consent form will be retained at the study team base. A copy of the consent form will be filed in the medical notes at each study site and a further copy given to the participant. The schedule of events is shown in Table 1 lists the assessments at each study time point, with a further detailed study summary in Fig. 1.

**Table 1 Tab1:**
[figure not shown]
Activate schedule of enrolment, interventions and assessments

**Fig 1 Fig1:**
[figure not shown]
Study Summary

Due to the nature of this study and its small size, we plan for the information sheet and consent form to be available only in English. However, interpreters and translation of written material will be considered should a potentially eligible patient require this.

### Loss of capacity to consent to research during participation in the study

The participants in this research study will be stroke patients. It is possible that they may temporarily (e.g. because of intercurrent illness) or permanently (e.g. because of further stroke) lose the capacity to consent to this research project. In either case, it is unlikely that they will be able to continue to participate in a study which involves self-directed practice. In the event of likely temporary incapacity, the ‘intervention’ or ‘control’ treatment will be stopped whilst the participant is unwell but restarted on recovery if the participant wishes to continue. In the event of permanent incapacity, the participant will be withdrawn from the study. Data collected prior to withdrawal will be retained and used in the study analysis as documented in the patient information sheet.

### Study treatments

#### Development of intervention

To develop the ARC intervention we undertook user workshops and an acceptability before and after study. We conducted two user workshops with healthcare professionals and stroke survivors exploring the choice of study metronome, study intervention and control treatment programme content, design of participant handouts/videos and study inclusion/exclusion criteria. Some issues were highlighted, for example clarity with regard to the inclusion/exclusion criteria, and changes implemented accordingly prior to commencement of the before and after study.

Twelve stroke survivors took part in the before and after study (eight receiving the intervention treatment and four receiving the control treatment programme). The study tested the study intervention and control treatment programmes proposed for the main pilot RCT and research protocols including outcome assessment. The treatment and research protocols were feasible and acceptable to stroke participants and providers. Adherence to the intervention was good, and no intervention-related adverse events were reported. The results of the user workshops and the before and after study have informed the design of the ACTIVATE pilot RCT.

### Study intervention treatment: auditory rhythmical cueing and gait and balance exercises

#### Dose and duration

Participants will be asked to undertake three × 30-min ARC treatment sessions per week for 6 weeks (total 18 sessions). This dose and duration has been selected based on findings from previous laboratory-based studies investigating cueing after stroke [11] and on findings from our previous successful RCT in Parkinson’s disease [24].

#### Materials

An auditory rythmical cueing device will be used. The auditory rythmical cue will be delivered through the metronome/phone speaker or through an earpiece attached to the metronome or phone. Depending on the participants’ choice, they will be provided with either a standard metronome (Metro Tuner MT-100 by Musedo with a tempo range of 30–250 bpm) or they will be shown how to download a free metronome app onto their phone (‘ZyMi Metronome’ for the Android operating system or ‘Pro Metronome’ for IOS).

#### Manuals

Participants will be provided with both paper- and web-based password-protected video-based training manuals on how to undertake the ARC treatment. Participants will also be given an exercise and falls diary.

#### Procedures

During the 6-week treatment programme, participants will be taught how to safely undertake a variety of balance and gait exercises using the ARC device (see Table 2 for examples of balance and gait exercises). The ARC treatment will gradually be progressed over the course of the 6 weeks. In the first session, the treatment provider will show the participant how to use the ARC device and at what frequency the ARC device should be set. The frequency of the auditory cue will be dependent on the type of exercise and the needs of the participant. During walking, the metronome frequency will initially be set at the participant’s self-selected stepping frequency as this has been shown to be the most effective method of cueing in stroke [25]. The auditory cue will have a regular pattern. Each step will be cued, rather than only the affected or unaffected lower limb, as this approach has been shown to lead to stronger auditory motor synchronisation [15]. A single tone rather than a separate tone to cue both legs will be used as this approach has been found to be most preferable in stroke [26].

**Table 2 Tab2:** Examples of exercises included in the ARC training programme

Exercise	Repetitions/time	Progressions
**Balance exercises**		
1. **Weight shift side to side with ARC device**	3 × 10	• Without holding on • Increase the cueing frequency by 5% to work on speed • Reduce the cueing frequency by 5% to work on control • Work on movement selectivity
2. **Weight shift forward and back with ARC device**	10 with the left foot in front 10 with the right foot in front	• Without holding on • Increase the cueing frequency by 5% to work on speed • Reduce the cueing frequency by 5% to work on control
3. **Stepping forwards and backwards with ARC device**	10× forward and back with both feet leading with the right leg 10× forward and back with both feet leading with the left leg	• Without holding on • Increase the cueing frequency by 5% • Reduce the cueing frequency by 5% to work on control
4. **Side stepping with ARC device**	Continue side stepping for 2 min	• Without holding on • Increase the cueing frequency by 5% • Reduce the cueing frequency by 5% to work on control
5. **Turning 180° in both directions with ARC device**	5× in one direction 5× in the other direction	• Increase the cueing frequency by 5% • Reduce the cueing frequency by 5% to work on control • Increase the number of repetitions • Work on the quality of the movement pattern Balance training Walking
6. **Turning 360° with ARC device**	3× in one direction 3× in other direction	• Increase the cueing frequency by 5% • Reduce the cueing frequency by 5% to work on control • Increase the number of repetitions
7. **Forward stepping onto a step with ARC device**	10× forward and back with both feet leading with the right leg 10× forward and back with both feet leading with the left leg	• Increase the cueing frequency by 5% • Reduce the cueing frequency by 5% to work on control • Increase the number of repetitions
8. **Side stepping onto a step with ARC device**	10× stepping both feet onto the step and onto the other side and returning to start position	• Increase the cueing frequency by 5% • Reduce the cueing frequency by 5% to work on control • Increase the number of repetitions
